### 4.3 Exclusion criteria

A potential subject who meets any of the following criteria will be excluded from participation in this study:

- severe cognitive impairment according to the patient's GP
- serious co morbidity that precludes participation in an exercise program
- current enrolment in interfering study
- if the patient's GP deems participation of the patient in this study undesirable and/or if participation could damage the doctor-patient relationship for any reason. The GP's judgement in relation to possible damage of the doctor-patient relationship will always overrule other in- or exclusion criteria.

### 4.4 Sample size calculation

#### Intervention study

The sample size calculation for our intervention study is based on the difference in 1-year DHI score change between the high-risk intervention group and the high-risk usual care group. We consider a DHI score difference of 12 or more to be a clinically relevant difference. The mean DHI score of patients above 65 consulting their GP because of dizziness is 36.3 with a standard deviation of 19.9. In order to detect a clinically relevant

difference with  $\alpha=0.01$  and  $\beta=0.90$  we used the following formula to calculate the sample size:

$$n = 2(2.58+1.28)^2 \cdot S^2/D^2$$

With  $n$  = number of patients,  $S$  = standard deviation,  $D$  = clinically relevant difference

A group size of  $n=82$  is sufficient  $(2(2.58+1.64)^2 \times 19.92^2/12^2)^{29}$ . However, we need to apply an extra correction since the proposed study is a cluster randomised trial. The correction that needs to be applied by performing an cluster randomised trial can be calculated with the following formula:

$$n = 1+(k-1) \cdot \rho$$

With  $n$  = number of patients,  $k$  = cluster size,  $\rho$  = intra-class correlation (ICC)

Based on secondary analysis of DIEP data we expect a cluster size of 5 patients per practice. An ICC of 0.01 is often used in sample size calculation in primary care research. However, we used an ICC of 0.05 to get a more conservative sample size. The correction factor for performing a cluster randomised trial is 1.2  $(1+(5-1) \cdot 0.05)$ . This means that a groups size of  $n = 99$   $(1.2 \cdot 82)$  is sufficient. Taking into account a loss to follow-up of 20% we need 124 participants in each arm. Thus, a total of 250 patients will be included in the intervention study.

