### 4.2 Inclusion criteria

In order to be eligible to participate in this study, a subject must meet all of the following criteria:

- being 65 years or older
- consulted a general practitioner for a new episode of dizziness, defined as recurrent dizziness for at least one month, including a giddy or rotational sensation, loss of balance, faint feeling, light-headedness, instability, or tendency to fall
- current dizziness-related impairment (DHI  $\geq$  30)
- ability to speak, read and write Dutch

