#### Validation study

The aim of the validation study is to validate a previously developed risk-score. This risk-score consists of 7 predictors and was constructed to predict the risk of chronic dizziness with persistent impairment (this means a DHI score  $\geq 30$  at 6 months follow-up).

A commonly used rule of thumb to judge sample sizes for developing diagnostic and prognostic models is the recommendation of at least 10 events per variable. This rule is based on estimates of the stability of coefficient estimates for individual variables in the model. According to this rule, at 6 months follow-up at least  $7 \cdot 10 = 70$  patients need to suffer from dizziness with a DHI-score  $\geq 30$  to enable validation of the risk-score. Based on secondary analysis of DIEP data we expect that 60% of the patients with a DHI  $\geq 30$  at baseline will have a DHI score of  $\geq 30$  at 6 months follow-up. Additionally to the validation of the previous developed risk score, we anticipate to model some 10-15 candidate variables to construct a new risk-score. With sample sizes of 125 patients in group A and 125 patients in group B we will be able validate the previous developed risk

score and we will be able to construct a new risk score with 15 predictors in impaired dizzy patients ( $0.6 * 250 = 150$ ,  $150/10 = 15$ ).

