## 8. METHODS

### 8.1 Study parameters/endpoints

#### 8.1.1 Main study parameter/endpoint

The primary clinical outcome is dizziness related impairment, which will be assessed using the DHI. For the validation study we will dichotomize all DHI scores. In the intervention study we will use the difference in the 1-year DHI score change between patients in the intervention group and patients in the control group.

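### The sample size is stated for the 1-year DHI change in patients with DHI of at least 30, but its SD of 19.9 is that of a single DHI score in all older dizzy patients, so the 90% power is not derived for the stated comparison

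*Protocol*

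**What the plan says.** Section 4.4 (Intervention study) describes the calculation as "based on the difference in 1-year DHI score change between the high-risk intervention group and the high-risk usual care group". Section 8.1.1 fixes the same endpoint for the trial: "we will use the difference in the 1-year DHI score change between patients in the intervention group and patients in the control group". The target difference is 12 points: "We consider a DHI score difference of 12 or more to be a clinically relevant difference".

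The SD comes from the sentence "The mean DHI score of patients above 65 consulting their GP because of dizziness is 36.3 with a standard deviation of 19.9". It enters the two-sample formula as S.

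Section 4.2 limits entry to patients with "current dizziness-related impairment", defined there as DHI of at least 30. Section 3 restricts the intervention study further, to those who also have at least one of the three treatable risk factors.

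The protocol gives no SD of DHI change, no correlation between baseline and 12 months and no SD for patients with DHI of at least 30. Nor does it say that 19.9 stands in for any of these.

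**The concern.** The SD does not match the comparison in two ways.

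- **Quantity.** 19.9 describes the spread of one DHI score between patients. The comparison is of change within patients, and the SD of a change depends on how strongly the two scores correlate.
- **Population.** 19.9 with a mean of 36.3 describes older patients consulting for dizziness, whatever their DHI. The trial admits only those at 30 or above.

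What is at stake is the power statement for the primary comparison. As written, a reader cannot tell whether 125 per arm gives 90%, less or more.

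**Working it through.** **Inputs from section 4.4.** D = 12; S = 19.9; two-sided alpha 0.01 (z = 2.58); power 90% (z = 1.28); cluster size 5; ICC 0.05; loss 20%; total 250, so 125 per arm.

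**The plan's own figure.**
- 2 × (2.58 + 1.28)² × 19.9² / 12² = 81.9, so 82.
- Design effect 1 + 4 × 0.05 = 1.2; 1.2 × 82 = 98.4, so 99.
- 99 / 0.8 = 123.75, so 124.

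The printed chain reproduces, and 19.9 drives it. (The substituted expression prints 1.64 in place of 1.28. That would give 98, so 82 came from 1.28. This is a separate slip.)

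**Can 19.9 describe the enrolled patients at baseline?** For scores confined to 30–100 with mean 36.3, the largest possible SD is √(6.3 × 63.7) = 20.0, reached only if every patient scores exactly 30 or exactly 100. So the source population must in practice include patients below 30. Under a normal model the share below 30 is Φ((30 − 36.3)/19.9) = Φ(−0.317) = 38%. The part at or above 30 then has mean 48.4 and SD 13.2.

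**SD that 90% power requires.** Effective patients per arm: 125 × 0.8 / 1.2 = 83.3. Largest SD for 90% power: 12 × √(83.3/2) / (2.576 + 1.282) = 20.1.

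**Power over a range of correlations.** The protocol gives no correlation, so r is an assumption. It is the baseline-to-12-month correlation before selection at 30. The model assumes bivariate normal scores, SD 19.9 at both times before selection, and a baseline cut at 30.

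- Unadjusted change: SD = √[(1 − r)² × 13.2² + 19.9² × (1 − r²)]
- Baseline-adjusted: residual SD = 19.9 × √(1 − r²)
- Power = Φ(12 / (SD × √(2/83.3)) − 2.576)

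| r | SD of change | Power, unadjusted change | Residual SD | Power, baseline-adjusted |
|---|---|---|---|---|
| 0 | 23.9 | 75% | 19.9 | 91% |
| 0.2 | 22.2 | 82% | 19.5 | 92% |
| 0.3 | 21.1 | 86% | 19.0 | 93% |
| 0.4 | 19.9 | 91% | 18.2 | 95% |
| 0.5 | 18.4 | 95% | 17.2 | 97% |
| 0.7 | 14.8 | 99.6% | 14.2 | 99.8% |

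If selection is ignored and the SD is 19.9 at both times, the SD of change is 19.9 × √(2(1 − r)). This equals 19.9 at r = 0.5 and is 25.2 (power 69%) at r = 0.2.

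For an unadjusted change, the stated 90% therefore needs r of at least about 0.4 with the cut at 30, or about 0.5 without it.

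**The case against.** The strongest reply is that 19.9 is conservative. If the final model adjusts for baseline DHI, the residual SD cannot exceed the 12-month SD. With that SD no larger than 19.9, power is at least 90% at every correlation. Section 10.1 plans a repeated-measures mixed model adjusted for potential confounders. It neither names nor excludes baseline DHI, and the analysis plan may settle that. This stands, and it means that no shortfall can be claimed. It does not repair section 4.4, which describes a comparison of change and does not offer 19.9 as an upper bound for anything.

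A reader might infer that the trial is underpowered, or that its power lies well below 90%. The documents do not support that. In the model with the cut at 30, the 75% figure needs zero correlation between two administrations of the same scale to the same patients, and no adjustment for baseline. The target is also strict: at two-sided alpha 0.05, even an SD of 23.9 gives 12 / (23.9 × √(2/83.3)) − 1.96 = 1.28, or about 90%. The ICC of 0.05 was itself chosen as cautious. These points limit the practical consequence, but the stated target remains alpha 0.01.

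A reader might also infer that the sponsor already holds the SD of 1-year change, because the validation part of section 4.4 says "Based on secondary analysis of DIEP data we expect that 60% of the patients" with DHI of at least 30 at baseline will still be at that level at 6 months. That figure is dichotomised and stops at 6 months. Nothing in the protocol shows that the earlier cohort measured DHI at 12 months.

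Finally, the range depends on the model. The DHI is bounded at 0 and 100, the two SDs may differ, and the further high-risk selection is ignored. The percentages are illustrative. The mismatch itself needs no model.

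**Conclusion.** The point holds as an unsupported input to the power statement, not as an arithmetic error and not as proof that 250 patients are too few. The chain 82, 99, 124 is computed correctly, but from an SD that is neither that of the 1-year change nor that of patients with DHI of at least 30.

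At 125 per arm the SD of change must not exceed about 20.1 for 90% power. For correlations of 0.2 to 0.7, an unadjusted change has power of about 82% to 99.6% under the normal model with baseline cut at 30. A baseline-adjusted comparison has at least 90% throughout, provided the 12-month SD is no more than 19.9. The direction of any error is therefore unknown. The protocol should be corrected, because the figure concerns the primary comparison and the correction is cheap.

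**What to change.** Revise the intervention-study paragraph of section 4.4 in one of two ways.

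1. Replace 19.9 with an SD that belongs to the comparison in patients with DHI of at least 30. If the earlier cohort holds usable scores, its 6-month change SD, or its residual SD after baseline adjustment, can serve as a labelled proxy. Otherwise, state an SD and a correlation as assumptions and show the power over a range of correlations.
2. Name the primary comparison as adjusted for baseline DHI, in sections 4.4 and 10.1 alike. State that 19.9 is taken as an upper bound for its residual SD, on the assumption that the 12-month SD does not exceed it.

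In either case, restate the power of 125 per arm with the same alpha, difference, design effect and loss.

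The cost is one rewritten paragraph, plus a short secondary analysis if the earlier cohort's 6-month scores can be used. The downside is that the stated power may become less favourable. No extra patients and no change of endpoint are needed.

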#### Validation study

The aim of the validation study is to validate a previously developed risk-score. This risk-score consists of 7 predictors and was constructed to predict the risk of chronic dizziness with persistent impairment (this means a DHI score  $\geq 30$  at 6 months follow-up).

A commonly used rule of thumb to judge sample sizes for developing diagnostic and prognostic models is the recommendation of at least 10 events per variable. This rule is based on estimates of the stability of coefficient estimates for individual variables in the model. According to this rule, at 6 months follow-up at least  $7 \cdot 10 = 70$  patients need to suffer from dizziness with a DHI-score  $\geq 30$  to enable validation of the risk-score. Based on secondary analysis of DIEP data we expect that 60% of the patients with a DHI  $\geq 30$  at baseline will have a DHI score of  $\geq 30$  at 6 months follow-up. Additionally to the validation of the previous developed risk score, we anticipate to model some 10-15 candidate variables to construct a new risk-score. With sample sizes of 125 patients in group A and 125 patients in group B we will be able validate the previous developed risk

score and we will be able to construct a new risk score with 15 predictors in impaired dizzy patients ( $0.6 * 250 = 150$ ,  $150/10 = 15$ ).

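### At ten outcomes per variable, 250 patients support at most about 10 predictors for a new risk score, and 8 with 20% loss, not the stated 15

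*Protocol*

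**What the plan says.** The validation-study part of Protocol section 4.4 adopts "the recommendation of at least 10 events per variable" as its criterion and gives the reason: "This rule is based on estimates of the stability of coefficient estimates for individual variables in the model". From the earlier cohort, "we expect that 60% of the patients with a DHI" of at least 30 at baseline will still score at least 30 at 6 months.

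Besides validating the existing 7-item score, "we anticipate to model some 10-15 candidate variables to construct a new risk-score". The conclusion starts "With sample sizes of 125 patients in group A and 125 patients in group B" and states that "we will be able to construct a new risk score with 15 predictors in impaired dizzy patients". The bracketed calculation behind it takes 60% of 250 to get 150 and divides by 10 to get 15. No allowance for loss to follow-up enters it.

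The intervention-study part of the same section does allow for loss: "Taking into account a loss to follow-up of 20% we need 124 participants in each arm". Section 3 places group B, the high-risk usual-care patients, in both studies.

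**The concern.** The calculation counts the more frequent outcome. With 60% expected to remain impaired, the event is the majority class and the 40% who fall below a DHI of 30 are the scarce one. In a logistic model, swapping the labels of event and non-event only reverses the signs of the coefficients. A capacity justified by coefficient stability must therefore be the same whichever outcome is called the event. The protocol's count breaks this: the same 250 patients would support 15 predictors for persistent impairment and 10 for its absence.

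The calculation also treats all 250 enrolled patients as having a 6-month outcome, while half of them (group B) are expected to lose members in the calculation for the intervention study.

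What is at stake is the quality of any new score. With too few limiting outcomes per variable, unpenalised coefficients are unstable and on average too large, so high predicted risks come out too high and low ones too low.

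**Working it through.** **Inputs**
- N = 125 + 125 = 250 enrolled (section 4.4, Validation study).
- Expected proportion with a DHI of at least 30 at 6 months: p = 0.60 (same place).
- Criterion: 10 per variable (same place).
- Loss to follow-up: 20% (section 4.4, Intervention study, where the outcome is the 1-year DHI change). No rate is given for the 6-month validation outcome or for group A, so 0% to 20% is shown.

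**The protocol's own figure**

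0.60 × 250 = 150, and 150 / 10 = 15. The arithmetic reproduces, but only with the larger class and zero loss.

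**Counting the smaller class**

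Supported predictors = min(p, 1 − p) × N × (1 − loss) / 10.

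| Loss by 6 months | Followed | With outcome (60%) | Without outcome (40%) | Supported predictors | Limiting outcomes per variable at 15 predictors |
|---|---|---|---|---|---|
| 0% | 250 | 150 | 100 | 10 | 100/15 = 6.7 |
| 10% | 225 | 135 | 90 | 9 | 90/15 = 6.0 |
| 20% | 200 | 120 | 80 | 8 | 80/15 = 5.3 |

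**Loss alone, keeping the protocol's count of events**

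0.60 × 200 = 120, and 120 / 10 = 12. Fifteen would then need 250 / 0.8 = 312.5, that is 313 enrolled.

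**Sample needed for 15 predictors on the smaller class**

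150 / 0.40 = 375 followed, or 375 / 0.8 = 468.75, that is 469 enrolled with 20% loss.

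**Sensitivity to the 60%**

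| p | No loss | 20% loss |
|---|---|---|
| 50% | 12.5 | 10 |
| 60% | 10 | 8 |
| 70% | 7.5 | 6 |

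A 50% outcome is the most favourable case, and even there the limit does not reach 15.

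**What over-fitting would look like**

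A simulation of unpenalised logistic models illustrates the consequence. It assumes independent, equally strong, normally distributed predictors, a 60% outcome and 200 patients followed. These are assumptions, apart from the 60% and the AUC of 0.80 that section 1 reports for the existing score. The calibration slope in new patients is 1.0 when predictions are neither too extreme nor too flat.
- True AUC 0.80: mean slope about 0.70 with 15 predictors, about 0.85 with 8.
- True AUC 0.70: about 0.55 with 15 predictors, about 0.75 with 8.
- With a 40% outcome in place of 60%, the slopes are nearly the same. This agrees with the argument that the label of the event does not matter.

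**Effect on validating the 7-item score**

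The protocol asks for 7 × 10 = 70 patients with the outcome. After 20% loss, 120 with the outcome and 80 without it remain, so the requirement is met on either count.

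**The case against.** Several points on the other side are fair.

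- **The arithmetic is right, and the rule as worded counts events.** Both are true. Read literally, with DHI of at least 30 as the event, the rule gives 15. The protocol does not itself say to count the smaller class. That follows from the reason it gives for the rule, coefficient stability, which does not depend on which outcome is named the event. This is a fault of method, not a slip in calculation.
- **The 20% belongs to another outcome.** This stands. It is stated for the intervention study at 1 year. A reader might infer that the sample supports only 8 predictors; the documents do not support 8 as a fixed figure. It is one end of a range from 8 to 10. The 10 needs no loss rate at all.
- **The 60% may not hold in this sample.** This also stands. It was estimated for impaired patients in general, whereas groups A and B are fixed at 125 each. The limit moves with the proportion but stays below 15.
- **The lower end of the planned range passes.** Ten candidates meet the criterion if nobody is lost. The stated capacity of 15 is what fails.
- **Multiple imputation (section 10) and bootstrapping (section 10.1) are planned.** Imputation adds no observed outcomes. The bootstrap is described as correcting the reported performance of the model, under validation of the 7-item score, and nothing says that coefficients of a new score will be shrunk. Neither restores 15.
- **Ten per variable is only a rule of thumb.** The protocol calls it that. But it is the only justification offered for the 15.

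**Conclusion.** The stated capacity of 15 predictors is wrong. On the protocol's own 60% and ten per variable, 250 patients support at most 10 predictors with no loss, 9 with 10% loss, and 8 if 20% are lost by 6 months. Counting the larger class does not rescue the figure once 20% loss is allowed, since that gives 12. At 15 predictors there would be 5.3 to 6.7 limiting outcomes per variable, about half to two thirds of the criterion.

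The limit of 10 rests on the 60% alone; the limit of 8 also rests on carrying the 20% over to 6 months and to group A.

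Two stronger readings are tempting and are not supported. A reader might infer that a new score is bound to fail in new patients. Falling short of a rule of thumb shows that an unpenalised score would be over-fitted and its predictions too extreme, which is less than failure. A reader might also infer that the main aims are undermined. They are not: a new score is not among the objectives in section 2, the requirement of 70 for validating the 7-item score is met, and the intervention comparison does not use this calculation. The severity is moderate.

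**What to change.** Replace the claim of 15 in section 4.4 with a limit counted on the smaller outcome class: at most about 10 candidate parameters for a new score, or 8 if 20% of patients are lost by 6 months. State the loss rate assumed at 6 months, and fix the candidate list before outcomes are examined.

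If the team wants to keep 10–15 candidates, commit to penalised (shrinkage) estimation and label the new score exploratory.

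Either change means rewriting a sentence or two and needs no extra patients. The cost of the first is real: if the seven existing predictors are kept as candidates, a limit of 10 leaves room for three new ones and a limit of 8 for one. The cost of the second is a weaker claim for the resulting score.

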## 5. TREATMENT OF SUBJECTS

### 5.1 Investigational treatment

All patients of the intervention group (group C, n=125) will receive one, two or three interventions. The interventions are based on three treatable risk factors for chronic dizziness with persistent impairment. The three risk factors are: usage of  $\geq 3$  Fall Risk Increasing Drugs (FRIDs), anxiety/depression, and impaired functional mobility.

Medication adjustment will be offered in case of the usage of  $\geq 3$  FRIDs, stepped-care will be offered in case of anxiety/depression and exercise therapy will be given in case of impaired functional mobility. All three interventions are evidence based and usual care for the above-mentioned risk factors.

Based on secondary analysis of DIEP data, we estimate that 62% of patients in the intervention group will be eligible to receive medication adjustment, 48% to receive stepped-care, and 37% to receive exercise therapy. Additionally, we estimate that 62% of patients in the intervention group will be eligible to receive only one intervention, 28% to receive two interventions, and 9% to receive all three interventions.

#### 1. Medication adjustment

Dizzy patients using  $\geq 3$  FRIDs will be subjected to a FRID-analysis. The list of FRIDs include psychotropic drugs (sedatives, antidepressants, neuroleptics), cardiovascular drugs (antihypertensives, nitrates, anti-arrhythmics, nicotinic acid,  $\beta$ -adrenoceptor blocker eye drops) and other drugs (analgesics, antivertigo preparations, hypoglycaemics, urinary antispasmodics). Interventional studies demonstrated a reduction in falls and postural instability following FRID-withdrawal.

All study patients will be asked about medication use during baseline assessment. After baseline assessment current prescribed medication will be requested from the patients pharmacist. The medication list will be sent by fax to the researcher. The patient will receive a phone call by the researcher for extra clarification if there is a discrepancy between the medication list supplied by the patient and the medication list supplied by the pharmacist.

Once a month, a trained pharmacist and an independent GP will have a meeting to review the FRID use of all patients of the intervention 'medication adjustment' that have been included in the preceding month. In every individual patient of group C, all potential FRIDs will be considered for withdrawal. If a FRID is considered redundant, the pharmacist and GP will advise to stop it. If a FRID is considered necessary, the pharmacist and GP will advise to change to another drug that sorts the same effect, or to reduce the dosage if considered safely possible. The results of the FRID-analysis, including considerations for

discontinuation/withdrawal of FRIDs, will be handed to the patients GP and practice nurse by fax. The practice nurse will invite the patient for a consultation with his/her GP within two weeks. The GP will discuss the outcomes of the FRID-analysis with the patient and will stop or withdrawal the FRIDs if the patient agrees. The GP will fill out a small questionnaire to give feedback about adjustment of medication to researcher.

If discontinuation or withdrawal of FRID appears to be impossible, the GP and the patient will receive a letter of the researcher.

